**Methods:**

This study is a randomized, parallel, and controlled trial, consist of a 6-week treatment period along with a 12-week follow-up period. Eighty-eight patients diagnosed as PPD will be recruited. They will be randomly assigned to one of two groups, internet-based peer education (IPE) group and regular health education (RHE) group, in a 1:1 ratio. Both groups will receive RHE along the 6-week treatment, while subjects in IPE group will receive 6-week online peer education additionally. The primary outcome is the response rate based on scores of 17-item Hamilton Depression Rating Scale at the week 6 and 12. The secondary outcomes include Edinburgh Postpartum Depression Scale (EPDS), World Health Organization Quality of Life Scale Brief (WHOQOL-BREF) and Self-Efficacy to Manage Chronic Disease Scale (SEMCD). All these scales will be evaluated at baseline, 1, 2, 4, 6, and 12 weeks after the initiation of intervention.

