### Sample size

2.9

The sample size has been calculated according to the results from a previous clinical trial (27). The primary outcome in present study is the response rate at the end of 6-week intervention. Referring to the study of Uebelacker et al. (27), the response rate of health education group is 28.3% (responders). This study assumed that the effective rate of IPE combined with RHE was 70%. A two-sided test is required (25), *α* = 0.05, the sample size ratio of the two groups N1: N2 = 1:1 (i.e., the number of cases in the two groups is equal), *β* = 0.2, and the power of the test is 1-*β* = 80%. The analysis result is N1 = N2 = 38 cases, and 44 cases are included in each group according to the dropout rate of 15%. Therefore, a total of 44 patients/group ×2 groups = 88 patients will be included in this study.

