### Statistical analysis plan

2.10

The statistical analysis will be conducted by independent statisticians who will be blinded to group allocation and intervention methods. Before data analysis, the research group will draw up a statistical plan, including the required data and method of data processing. For Categorical data, we performed the Chi-square (x^2^) test for between-group differences. For continuous and normally distributed data, we performed Student’s *t*-test for between-group differences and paired t test for within-group differences. If data were distributed nonnormally, the Mann–Whitney U test for between-group differences and the Wilcoxon test for within-group differences would be used. The normally distributed data were expressed as the mean ± standard deviation. Nonnormally distributed data would be expressed as the median or interquartile range (IQR). For categorical variables, the X^2^ test will be used to examine the between-group differences, and percentages and frequencies will be presented to describe the effect size.

For longitudinal data analysis considering the repeated measurements at assessment nodes in this study, the Generalized Estimating Equations (GEE) model will be employed.

Fixed effects structure: It will include the group variable (experimental vs. control), time points (six assessment nodes as a categorical variable), and the interaction term between group and time points. Additionally, potential confounding variables (e.g., baseline characteristics that show imbalance between groups) will be incorporated into the model as covariates to adjust for their effects.

Correlation structure: Given the repeated measurements within individuals over time, the exchangeable (compound symmetry) correlation structure will be initially assumed, which posits that the correlation between any two measurements from the same individual is equal. Sensitivity analyses will be conducted using other correlation structures (e.g., autoregressive of order one, which assumes a higher correlation between measurements that are closer in time) to assess the robustness of the results. The working correlation matrix will be estimated based on the observed data during model fitting.

All clinical data analyses will be performed using SPSS V.22.0 software. Missing data will be handled using the multiple imputation method. A two-tailed test will be conducted, and a *p* < 0.05 will be considered statistically significant.

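### The six-visit GEE interaction test (5 df, 88 patients) has no stated small-sample correction; judged by an uncorrected robust Wald chi-square, its 5% level would be about 8%

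*Protocol article*

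**What the plan says.** Section 2.10 states that for the repeated measurements "the Generalized Estimating Equations (GEE) model will be employed". The model contains group, "time points (six assessment nodes as a categorical variable), and the interaction term between group and time points", plus covariates that turn out imbalanced at baseline. For the working correlation, "the exchangeable (compound symmetry) correlation structure will be initially assumed", and other structures, such as first-order autoregressive, serve as sensitivity analyses. The same section adds that "All clinical data analyses will be performed using SPSS V.22.0 software", that "Missing data will be handled using the multiple imputation method", and that "A two-tailed test will be conducted, and a *p* < 0.05 will be considered statistically significant".

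Section 2.9 fixes the size: "a total of 44 patients/group ×2 groups = 88 patients will be included in this study", built up from 38 per arm before an allowance for dropout. The Abstract gives the same total.

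The article does not name the variance estimator (robust or model-based), the test statistic (Wald or score) or its reference distribution, and it states no small-sample adjustment. It also does not say that the joint interaction test decides anything. The primary outcome (section 2.11) is HDRS17 response at week 6, and section 2.10 assigns categorical data to the chi-square test.

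**The concern.** A GEE with an assumed working correlation normally takes its standard errors from the sandwich estimator, which is biased downwards when the number of independent units is modest. The Wald statistic is then usually compared with a chi-square, as though the variance matrix were known. Both shortcuts cost little for one contrast. The cost grows with the number of contrasts tested jointly, because a whole covariance matrix is being estimated from the same patients. Coding six visits as a factor makes the interaction a five-dimensional test on 88 patients.

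The planned sensitivity analyses change only the working correlation, so they do not correct the small-sample behaviour of the sandwich.

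At stake is the longitudinal evidence on HDRS17, EPDS, WHOQOL-BREF and SEMCD scores. If a significant interaction were reported at p < 0.05 from the uncorrected joint test, it would arise by chance about one and a half times as often as the stated level implies (7.8/5 = 1.6).

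**Working it through.** **Inputs.** Two arms and six categorical visits (2.10); 44 per arm randomised and 38 per arm before the dropout allowance (2.9); two-sided 0.05 (2.10). The 38 is taken as stated; whether it follows from the assumed response rates is a separate question and does not enter here.

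**Assumption, not in the article.** The joint interaction is tested by the uncorrected robust Wald statistic against chi-square.

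**Degrees of freedom.** (2 − 1) × (6 − 1) = 5. The 5% chi-square cut-off is 11.07.

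**Exact size under normality.** With complete data the group-by-visit model is saturated. The robust Wald statistic W is then a quadratic form in the five between-arm differences in change from baseline, with covariances computed using divisor n instead of n − 1. For n per arm and equal covariances, W = T² × n/(n − 1), where T² is Hotelling's statistic and T² ~ [5(2n − 2)/(2n − 6)] × F(5, 2n − 6).

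- 44 per arm: 11.0705 × 43/44 × 82/(5 × 86) = 2.063, and P[F(5, 82) > 2.063] = **7.8%**.
- 38 per arm: 11.0705 × 37/38 × 70/(5 × 74) = 2.039, and P[F(5, 70) > 2.039] = **8.4%**.
- Using divisor n − 1 alone lowers these only to 7.2% and 7.6%, so most of the excess comes from the chi-square reference.
- Cut-off on W that gives exactly 5% at 44 per arm: F(0.95; 5, 82) = 2.326, and 2.326 × 430/82 × 44/43 = 12.48, instead of 11.07.

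**Single contrast (1 df).** 3.8415 × 43/44 = 3.754, and P[F(1, 86) > 3.754] = 5.6%. At 38 per arm it is 5.7%.

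**Simulation under no treatment effect, robust test, 5 df.**

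| Setting | 44 per arm | 38 per arm |
|---|---|---|
| Normal data, exchangeable or AR(1) truth | 7.8 to 8.0% | 8.2 to 8.5% |
| Skewed, or truncated integer scores like HDRS17 | 7.3 to 7.8% | 7.7 to 8.3% |
| Full exchangeable GEE fit, no dropout | 7.5 to 8.3% | not run |
| Full exchangeable GEE fit, 15% monotone dropout | 7.8 to 7.9% | not run |

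**Model-based exchangeable errors, 44 per arm, 20,000 null trials per setting.** If the truth is AR(1) by visit with correlation 0.6, 0.7 and 0.8, the 5-df test rejects in 6.8%, 7.5% and 7.9% of trials when the scale and correlation estimates are corrected for the number of parameters. Without that correction the figures are 7.5%, 8.3% and 8.8%. If the truth is exchangeable, they are 5.0% with the correction and 5.9% without.

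**Not modelled.** Multiple imputation and covariate adjustment, both planned in section 2.10.

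**The case against.** The strongest objection is that the criticised test is not in the article. Estimator, statistic and reference distribution are details that an article commonly leaves to the analysis plan, and section 2.10 says that a statistical plan will be drawn up before analysis. This stands to the extent that the figure of about 8% must be conditional. It does not remove the point. The article does fix the GEE, the six-level factor, the sample size and the 0.05 level, and both ordinary uncorrected ways of running that model miss 5% if correlation decays with time. Section 2.10 itself names such decay as an alternative worth checking.

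Second, a reader might infer that the trial's efficacy conclusion carries an 8% error rate. The documents do not support that. The hypotheses in the Introduction concern superiority directly after the intervention and at follow-up, which are single-time comparisons. Nothing makes the joint interaction a decision rule. The primary responder comparison falls under the chi-square test. Section 2.10 also lists simple two-group tests for continuous data, and section 3.1 promises a conservative reading of the self-reported secondary scales.

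Third, 8% is not the true error rate of the analysis as it will be run. Imputation changes both the variance and the reference distribution of a joint test, and added covariates change the model. The 38-per-arm figure is for completers, whereas imputation would keep dropouts in the analysis. These limits stand.

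**Conclusion.** The point holds in conditional form and concerns the longitudinal analysis only. With 88 patients and a 5-df interaction, an uncorrected robust Wald chi-square at nominal 5% has a size of about 7.8% (44 per arm) to 8.4% (38 per arm) for complete normal data, and the robust-test simulations with other distributions and with dropout stay close to that range. Model-based exchangeable errors are a remedy only if exchangeability is true; otherwise they run at about 7 to 8%, or nearly 9% in the least favourable setting tried. Single-visit contrasts, at 5.6 to 5.7%, are a minor matter.

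The conclusion rests on the assumption that no small-sample correction is applied. The article states none, but a separate analysis plan could. It is worth correcting because a better-calibrated method is readily available at little cost.

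**What to change.** In the statistical plan that section 2.10 promises:

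1. For HDRS17, EPDS, WHOQOL-BREF and SEMCD scores, name the week-6 and follow-up arm contrasts as the reported longitudinal results, in place of the joint 5-df interaction test.
2. State a small-sample method. Either use a linear mixed model with unstructured covariance and Satterthwaite or Kenward-Roger degrees of freedom, or keep the planned GEE with a bias-corrected sandwich variance and a t or F reference.
3. Name the variance estimator and test statistic, and check that the chosen software version offers them.

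No change is proposed for the binary week-6 response, which the plan assigns to the chi-square test.

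The cost is some plan wording and possibly a different procedure, with slightly wider intervals and larger p-values. Design, data collection and sample size are untouched.

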### Primary outcome

2.11

The response rate based on 17-item Hamilton Depression Rating Scale (HDRS17) score at week 6 is considered primary outcomes. Response rate is defined as the percentage resulting from the dividing of the scores at baseline from the difference between those of baseline and week 6. The response rate reaches or over 50%, the patient will be defined as a responder; otherwise, the other patients will be considered non-responders. The formula for calculating the response rate is as follows:

$$\text{Response Rate}=\frac{\left(\text{HDRS}17\;\text{score}\;\mathrm{at}\;8\mathrm{th}\;\text{week}-\text{HDRS}17\;\text{score}\;\mathrm{at}\;\text{baseline}\right)}{\text{HDRS}17\;\text{score}\;\mathrm{at}\;\text{baseline}}\times 100\%$$

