### Secondary outcome

2.12

(1) Edinburgh Postpartum Depression Scale (EPDS) (25). It is considered the most frequently validated instrument to screen for perinatal depression. The scale consists of 10 items, mainly concerning the factors like depression, anxiety, anhedonia and self-harm/suicide. Higher scores indicate more severe symptoms of postpartum depression.(2) World Health Organization Quality of Life Scale Brief (WHOQOL-BREF) (28). This standardized tool conceptualizes quality of life as personal perception. Physical health, psychological health, social interactions, and environment are the four dimensions that make up WHOQOL-BREF. There are three to eight items in per domain. Additionally, two generic questions on health satisfaction and overall quality of life (Q1 and Q2) are provided. With the exception of 3 items—pain and discomfort, the need for treatment, and negative feelings—each item is based on self-report and scored on a scale of one to five, with higher scores indicating higher quality of life.(3) Self-Efficacy to Manage Chronic Disease Scale (SEMCD) (29). This patient reported scale mainly evaluate symptoms of chronic conditions, functioning, and self-management. This self-efficacy scale for chronic disease patients was developed by Stanford University in the United States. The scale contains 6 items, each item ranging from 1 to 10, with 1 indicating no confidence at all and 10 indicating great confidence. The average score of the 6 items reflected the average level of self-efficacy of patients. A score of 1–3 indicates a low level of self-efficacy, a score of 4–7 indicates a medium level of self-efficacy, and a score of 8–10 indicates a high level of self-efficacy. Its Cronbach’sα coefficient is 0.91, with high reliability and wide application.

Scales information will be collected and managed by corresponding researchers, who are unaware of the group division. To exclude confounding factors, each subject will be evaluated by the same researcher in the duration of trial.

Evaluation time points: all scales will be evaluated at baseline, 1, 2, 4, 6, and 12 weeks after the initiation of intervention.

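### Section 2.10 picks GEE covariates by observed baseline imbalance, a rule that cannot change the group-by-time effect while T0 is an outcome node; pre-specified adjustment for the T0 score would be more precise

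*Protocol article*

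**What the plan says.** All of the following is in the protocol article.

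- **Model.** Section 2.10 (Statistical analysis plan): "For longitudinal data analysis considering the repeated measurements at assessment nodes in this study, the Generalized Estimating Equations (GEE) model will be employed". No outcome, distribution or link is named.
- **Fixed effects.** Group, "time points (six assessment nodes as a categorical variable), and the interaction term between group and time points".
- **Covariates.** In addition, "potential confounding variables (e.g., baseline characteristics that show imbalance between groups) will be incorporated into the model as covariates". No covariate is named, and no threshold or candidate list is given.
- **What the six nodes are.** Section 2.12 (Secondary outcome): "all scales will be evaluated at baseline, 1, 2, 4, 6, and 12 weeks after the initiation of intervention". Table 1 in section 2.8 agrees that every scale is taken at T0. Baseline is therefore one of the six nodes.
- **Binary data.** Section 2.10 assigns these to a chi-square test: "For categorical variables, the X^2^ test will be used to examine the between-group differences".
- **Primary outcome.** Section 2.11: "The response rate based on 17-item Hamilton Depression Rating Scale (HDRS17) score at week 6 is considered primary outcomes". The cut-off is relative to the patient's own baseline: "The response rate reaches or over 50%, the patient will be defined as a responder".

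**The concern.** Two features of the longitudinal model work against each other.

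First, the covariates are to be chosen by looking at which baseline characteristics differ between the arms. After randomisation such differences are chance. A variable earns its place in the model by predicting the outcome, and that can be judged in advance. Under the stated rule the model is unknown until the baseline data have been compared by arm, and the baseline score of the scale being analysed becomes a covariate only if it happens to look unbalanced.

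Second, T0 sits in the outcome vector. The treatment effect at week 6 is then the group-by-week-6 term, which is the difference between arms in change from T0. A fixed patient-level covariate added as a main effect shifts all six nodes equally, so it should drop out of that difference. If so, the adjustment the plan promises does nothing for the effect of interest, and precision available from T0 scores that are already collected is left unused.

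**Working it through.** The plan gives no figure of its own on this point, so there is none to reproduce. The inputs from the document are 44 patients per arm, six nodes including T0, an exchangeable working correlation, a two-sided 0.05 level, and week-6 response rates of 28.3% and 70% (section 2.9). The baseline-outcome correlation rho is not given; values of 0.3, 0.5 and 0.7 are assumed.

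**1. Does a baseline covariate alter the group-by-time effect?** Take an identity link, complete data and a covariate z with coefficient γ. Group, time and their interaction give each arm a free mean at each node. The fitted mean for arm g at node t, at z = 0, is therefore

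m(g,t) = ȳ(g,t) − γ·z̄(g).

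The second term does not depend on t. The group-by-week-6 term is

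[m(1,wk6) − m(1,T0)] − [m(0,wk6) − m(0,T0)] = [ȳ(1,wk6) − ȳ(1,T0)] − [ȳ(0,wk6) − ȳ(0,T0)],

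and γ has cancelled. In one simulated six-node data set (88 patients, complete data) the term was −2.653 (SE 0.666) with no covariate, with the baseline score added, and with an imbalanced age covariate added. On the same data, T1 to T5 with baseline as covariate gave SE 0.547; (0.547/0.666)² = 0.67, about one-third less variance.

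**2. Change contrast against baseline adjustment.** With equal variances σ² at T0 and week 6, and the same number per arm, the two effect variances are proportional to:

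- change from T0: 2σ²(1 − rho)
- adjusted for T0: σ²(1 − rho²)

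The ratio is (1 − rho²)/[2(1 − rho)] = (1 + rho)/2.

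| rho | 1 − rho² | 2(1 − rho) | ratio | variance saved |
|---|---|---|---|---|
| 0.3 | 0.91 | 1.40 | 0.65 | 35% |
| 0.5 | 0.75 | 1.00 | 0.75 | 25% |
| 0.7 | 0.51 | 0.60 | 0.85 | 15% |

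Simulated exchangeable GEEs on 88 patients with complete data gave savings of about 35%, 26% and 16%.

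**3. What does choosing by imbalance buy where a covariate can act?** This was checked on a single continuous post-baseline outcome, not the six-node model: 44 per arm, true effect 0.5 SD, 4,000 simulated trials per setting. The plan sets no threshold, so adjustment when baseline differs at p < 0.05 is an assumption.

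| rho | power, none | power, imbalance rule | power, always adjust | type I error, imbalance rule |
|---|---|---|---|---|
| 0.3 | 0.65 | 0.65 | 0.67 | 0.052 |
| 0.5 | 0.64 | 0.65 | 0.75 | 0.043 |
| 0.7 | 0.65 | 0.67 | 0.91 | 0.038 |

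The rule performs almost like no adjustment. It does not inflate type I error; at the higher correlations it is slightly conservative.

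**4. Can the six-node model be fitted?** On a simulated continuous score, yes: the fit was ordinary, with a group-by-week-6 SE of about 0.9. On binary response with a logit link, no. Response is change from T0, so both T0 cells are 0/44 and their log-odds are minus infinity. This was tried on 59 simulated data sets with every post-baseline cell non-empty, using the plan's week-6 rates and assumed rates at the other visits. The six-node fit gave intercepts of about −31 to −37, and SEs for the group-by-week-6 term and the week-6 contrast that were missing or huge in 59 of 59. With T1 to T5 only, 59 of 59 were usable (median week-6 log odds ratio 1.74, SE 0.47).

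**The case against.** The strongest reply is that keeping T0 as an outcome node is an accepted model. On HDRS17, EPDS, WHOQOL-BREF and SEMCD scores it can be fitted, it always uses the baseline value whether or not that looks balanced, and its interaction terms estimate a legitimate quantity. This stands: the point is about precision and pre-specification, not validity. The gain also depends on an unknown correlation and shrinks as that rises, to 10% at rho = 0.8 by the same formula. The power figures in step 3 concern a single outcome, so they show the weakness of the selection rule and do not measure a loss in the six-node model.

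A reader might infer that the plan's model cannot be fitted to the primary endpoint. The document does not support that. Section 2.10 never applies the GEE to response, names no logit link, and sends categorical data to the chi-square test; the primary outcome is response at one visit. The failure in step 4 arises only if someone also models response over all six nodes. A reader might also infer that the chi-square test ignores baseline. It does not, because each patient's responder status is defined relative to her own baseline score.

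It can also be said that imbalance is offered only as an example, that the statisticians are blinded, and that section 2.10 promises a statistical plan before analysis. Blinding limits the scope for favouring an arm but does not fix the model. A later plan could list covariates, but one that follows the rule as written still has to look at the data first.

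**Conclusion.** The point holds as a modest one. Section 2.10 states, rather than merely leaves open, a data-dependent covariate rule. With T0 as an outcome node and complete data, that rule leaves the group-by-time effect exactly as it was. The multiple imputation planned in section 2.10 would supply complete data if it covers every missing scale score. Modelling the post-baseline nodes with the T0 score as covariate would lower the variance of the scale effects by about 35%, 25% or 15% at rho of 0.3, 0.5 or 0.7, assuming equal variances over time. There is no evidence of inflated type I error, and nothing here invalidates the week-6 chi-square test or the six-node GEE on scores. The problem of empty T0 cells is conditional on a logit model of response, which the document does not specify; one sentence would rule it out.

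**What to change.** In section 2.10:

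- Delete the rule that admits covariates because they look unbalanced.
- For each scale, specify the GEE on T1 to T5 only, with arm, time, arm-by-time and the T0 value of the same scale as a covariate named in advance. Taking T0 out of the outcome vector avoids using baseline twice.
- State which outcomes the GEE serves, and that T0 is not a node in any model of response.
- Keep the week-6 chi-square test as the primary analysis. A logistic regression of week-6 response on arm and baseline HDRS17, with a 95% confidence interval, may be added as an optional supportive analysis.

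The cost is wording. Every scale is already collected at T0, so no new data, visits or patients are needed. The change should be made before anyone compares the arms at baseline.
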